|                                     | 
c) regular and correct use of a contraceptive method with an Pearl Index < 1% per year
 
d) sexual abstinence
 
e) vasectomy of the partner
                                                                                                                                                                                                                                                                                                                                                                                                                                                                                                                                                                                                                                                                                                                                                                                                                                                                                                                                                                                                                                                                                                                                                                                                                                                                                                                                                                                                                                                                                                                                                                                                                                                                                                                                                                                                                                                                                                                           |
| Course of the Clinical Trial | 
Screening (V-3; week 1 post-transplantation at the ward; latest until discharge)
 
 
• Informed consent
 
• Preliminary inclusion / exclusion criteria check
 
• Medical history
 
• Laboratory workup (TTV R-GENE®)
 
• Biobanking
 
 
Screening (V-2, V-1; at routine visits in month 2 and 3 post-transplantation)
 
 
• Laboratory workup (TTV R-GENE®; TAC-trough level; chemistry; complete blood count [CBC]; urine analysis)
 
• Biobanking
 
 
Visit 1 (day 0; after day 93 post-transplantation within month 4 post-transplantation)
 
 
• Inclusion/ exclusion criteria
 
• Medical history
 
• Medication
 
• Vital signs
 
• Physical examination, body weight
 
• Pregnancy test
 
• Laboratory workup (TTV R-GENE®; TAC-trough level; chemistry; CBC; venous blood gas analysis [vBGA]; urine analysis)
 
• Virology (BKV; cytomegalovirus [CMV])
 
• Biobanking
 
• DSA
 
• Quality of life (SF-36; MTSOSD-59R)
 
• Drug adherence (MEMS® BUTTON; patient diary; BAASIS; psychological evaluation)
 
• Data sampling concerning protocol biopsy performed according to local centre standard; protocol biopsy has to be performed before V1
 
• Intervention: adaption of TAC dose
 
 
Visit 2 (week 6; ± 14 days)
 
 
• Vital signs
 
• Medication
 
• AE
 
• Primary endpoint
 
• Laboratory workup (TTV R-GENE®; TAC-trough level; chemistry, CBC, vBGA; urine analysis)
 
• Virology (BKV; CMV)
 
• Biobanking
 
• Drug adherence (MEMS® BUTTON; BAASIS; patient diary)
 
• Intervention: adaption of TAC dose
 
 
Visit 3 (week 12; ± 14 days)
 
Like Visit 2
 
Visit 4 (week 18 ± 14 days)
 
Like Visit 2
 |

|                                          |                                                                                                                                                                                                                                                                                                                                                                                                                                                                                                                                                                                                                                                                                                                                                                                                                                                                                                                                                                                                |
|------------------------------------------|------------------------------------------------------------------------------------------------------------------------------------------------------------------------------------------------------------------------------------------------------------------------------------------------------------------------------------------------------------------------------------------------------------------------------------------------------------------------------------------------------------------------------------------------------------------------------------------------------------------------------------------------------------------------------------------------------------------------------------------------------------------------------------------------------------------------------------------------------------------------------------------------------------------------------------------------------------------------------------------------|
|                                          | 
Visit 5 (week 24; <math>\pm</math> 14 days)
Like Visit 2
 
Visit 6 (week 30; <math>\pm</math> 14 days)
Like Visit 2
 
Visit 7 (final visit: week 36 <math>\pm</math> 14 days)
 
 
• Vital signs
 
• Physical examination, body weight
 
• Medication
 
• AE
 
• Primary endpoint
 
• Pregnancy test
 
• Laboratory workup (TTV R-GENE®; TAC-trough level; chemistry, CBC; vBGA; urine analysis)
 
• Virology (BKV; CMV)
 
• Biobanking
 
• DSA
 
• Drug adherence (MEMS® BUTTON; BAASIS; patient diary; claimed prescription check; psychological evaluation)
 
• Quality of life (SF-36; MTSOSD-59R)
 
• Data sampling concerning protocol biopsy performed according to local centre standard
 
 
Routine calls every second week will help to detect AE and infections treated outside the study centre.
 |
| Trial Specific Procedures         | 
 
• TTV quantification (no additional vein-puncture)
 
• Health-related quality of life questionnaires: SF-36, MTSOSD-59R
 
• Pregnancy test, physical examination, body weight and vital signs
 
• Patient diary
 
• DSA assessment (if not part of the routine post-transplant care; no additional vein-puncture)
 
• Assessment of month 12 protocol biopsy with 'molecular microscope' if performed as part of routine post-transplant care
 
• Additional adherence monitoring: MEMS® Buttons, BAASIS questionnaires, psychological evaluation and claimed prescription check
 
• Sub-study: biobanking of urine, whole blood (PAXgene), serum and plasma (no additional vein-puncture)
 
                                                                                                                                                                                                  |
| Investigational Medicinal Product | 
Active substance: TAC
 
Trade name: All products containing TAC and authorized in participating countries
 
Manufacturer: All manufactures of authorized products
                                                                                                                                                                                                                                                                                                                                                                                                                                                                                                                                                                                                                                                                                                                                                                                        |
| Treatment Schedule                | 
Active group
 
Product: TAC
 
Dose: Dependent on TTV level (target 4.6 to 6.2 log10 c/mL) quantified by real-time PCR kit TTV R-GENE® in the plasma
 
Duration: 9 months
 
Control group
 
Product: TAC
 
Dose: According to local centre standard
 
Duration: 9 months
                                                                                                                                                                                                                                                                                                                                                                                                                                                                                                                                                                                                                                                     |

|                          |                                                                                                                          |
|--------------------------|--------------------------------------------------------------------------------------------------------------------------|
| Including Centres | Berlin, Dresden, Graz, Grenoble, Groningen, Innsbruck, Leiden, Linz, Prague, Regensburg, Strasbourg, Valencia and Vienna |
| Grant Support     | H2020 RIA, 'TTV GUIDE TX', #896932, project coordinator Assoc. [name]. [name], PhD                            |

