| End points of the Clinical Trial          | 
Primary end point:
 
A composite of one of the following:
 
 
1. Infectious disease event (diagnosed on the basis of the Infectious Diseases Guidelines 2019 published by the American Society of Transplantation) requiring one of the following: 
 
a) Inpatient treatment (including day-care)
 
b) Application of anti-bacteria, fungal, viral and protozoal drugs (including increase of prophylactic treatment dose; therapy restricted to topical treatment of minor localised cutaneous disease is excluded)
 
c) Reduction of immunosuppression
 
 
 
 
SARS-CoV-2 positive antigen test or PCR with or without COVID-19 is excluded
 
 
2. Allograft rejection detected upon indication biopsy, based on the
 
                                                                                                                               |

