|                                   | 
Banff 2019 Kidney Meeting Report including borderline rejection suspicious for T-cellular mediated rejection (BL TCMR)
 
3. Death
 
4. Graft loss
 
Secondary end points:
 
 
• Single components of the primary outcome
 
• Episodes of infection and graft rejection defined by the treating medical personnel
 
• Severe infection (necessitating treatment in the inpatient or day-care ward) and severe rejection (excluding BL TCMR)
 
• All of the three mentioned secondary end-points including COVID-19
 
• Episodes of infection due to COVID-19
 
• Estimated glomerular filtration rate (eGFR; current CKD EPI and MDRD abbreviated)
 
• Rejection detected by protocol biopsy at month 12 post-transplantation: according to BANFF 2019 meeting report (including/excluding BL TCMR) and according to molecular microscope (MMDX)
 
• de novo donor specific antibodies (DSA)
 
• Plasma TTV load
 
• TAC trough level and dose
 
• Unchanged, increased, and decreased TAC trough target levels
 
• Health related quality of live: SF-36 and MTSOSD-59R questionnaires
 
• Drug adherence assessed according to paper-based assessment, MEMS® Buttons (AARDEX Group, Switzerland) on TAC blisters, BAASIS questionnaire, claimed prescriptions, psychological evaluation and TAC trough level variability
 
• Adverse Events and Serious Adverse Events (AEs/SAEs)
 
• Development of malignoma
 
 |

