## 5.11 BLINDING AND EMERGENCY ENVELOPES

### 5.11.1 BLINDING

The study will be conducted using a single-blind design (participants blinded). Assessors of the primary outcome will also be blinded to allocation: all episodes of infection and allograft rejection will be assessed by personnel blinded to the randomization code (infection: two infectious disease specialists; rejection: two kidney pathologist; Vienna based). The randomization code will be kept with the sponsor. No clinical staff member has access to the treatment randomization codes. Unblinding is not necessary due to the study design (investigator not blinded to allocation).

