### **Infections concerning endpoints (see 3.2 and 3.3)**

**Infectious disease workup will be performed according to local standards. However, some diagnostic workup should be performed to obtain comparable findings:**

- In case of suspected infection, the investigators should perform a minimum diagnostic set including CBC, CRP, blood pressure, heart rate, respiratory rate, and body temperature and document an altered mental status.

In addition the following diagnostic sets should be applied:

- In patients with fever: blood and urine cultures, urinary dip stick and CMV PCR from the blood.
- In patients with suspected urinary tract infection: urinary dip stick and urine cultures; if available ultrasound of the urinary track system.
- In patients with suspected respiratory infection: chest X-ray; if available: *legionella/ haemophilus* and *pneumococcus* urinary antigen and sputum or nasopharyngeal swab multiplex PCR.
- In patients with suspected diarrhea: stool cultures and CMV PCR from stool samples; if available: multiplex PCR from stool samples.

**In general, all performed supporting diagnostic tests related to infections should be documented** including vital signs (blood pressure, heart rate, respiratory rate, mental state, body temperature), laboratory (e.g. CBC, CRP, PCT, IL-6, creatinine/eGFR, blood urea nitrogen, blood pH, lactate, albumin), microbiologic and virologic results, imaging (e.g. X-ray, CT, MRI, PET, US, endoscopy), and qSOFA/SOFA score.

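### The primary endpoint excludes SARS-CoV-2 by test positivity although no diagnostic set requires the test, and the rule is silent on co-infection; define it by adjudicated cause and add the composite with COVID-19 counted

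*Protocol*

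**What the plan says.** **Exclusion.** The synopsis and section 3.2 carry the same line under component 1, infectious disease event: "SARS-CoV-2 positive antigen test or PCR with or without COVID-19 is excluded". A qualifying infection must otherwise need inpatient or day-care treatment (1a), antimicrobial drugs (1b) or reduced immunosuppression (1c).

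**Work-up.** Section 6.17 says "Infectious disease workup will be performed according to local standards", but adds that "some diagnostic workup should be performed to obtain comparable findings". The fever set reads: "In patients with fever: blood and urine cultures, urinary dip stick and CMV PCR from the blood". The respiratory set begins "In patients with suspected respiratory infection: chest X-ray; if available", and among the conditional items is "sputum or nasopharyngeal swab multiplex PCR". No set, including the general minimum set, names a SARS-CoV-2 test. Tests that are performed are to be documented.

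**Who knows the arm.** Section 5.11.1: "Unblinding is not necessary due to the study design (investigator not blinded to allocation". Infections are re-assessed by two blinded infectious disease specialists who must agree, working from data the sites enter in the eCRF (3.2). They may query the site (6.17).

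**COVID-inclusive endpoints.** The synopsis and 3.3 list "All of the three mentioned secondary end-points including COVID-19". The three are the single components, the episodes defined by treating personnel, and severe infection and rejection. COVID-19 episodes are also listed separately. Neither 3.3 nor the sensitivity analyses in 10.3.3 include the four-part composite with COVID-19 counted.

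**The concern.** The exclusion works through a test result, and the protocol does not standardise who gets the test. Take one treated respiratory illness caused by SARS-CoV-2. If it is tested, it leaves the primary endpoint. If it is not, it can stand as an infection meeting 1a-1c. Blinded assessors can reclassify what was recorded but cannot recover a test that was never taken.

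The staff who decide whether to test know the allocation. If arm T were tested more, more arm T events would be removed and non-inferiority would be easier to declare. If arm S were tested more, power would fall.

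The line also speaks of positivity, with or without disease, and gives no rule for co-infection. Two assessors could read it differently for a treated bacterial or CMV infection in a patient who also has a positive SARS-CoV-2 test.

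**Working it through.** **Inputs from the protocol.** Section 10.2: 120 evaluable patients per arm, rates 0.30 (T) and 0.40 (S), margin 10 points, one-sided alpha 2.5%, stated power 90.42%. Section 6.2: allocation 1:1.

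**The plan's own figure.** Power = Φ((0.10 − (0.30 − 0.40))/SE − 1.96), with SE = √((0.30×0.70 + 0.40×0.60)/120) = 0.0612. This gives Φ(3.266 − 1.960) = 90.42%, as stated. That figure does not depend on the SARS-CoV-2 rule.

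**Assumptions, none of them in the protocol.**
- c is the share of patients in each arm whose only qualifying event is a SARS-CoV-2 episode that would meet 1a-1c whether or not it was tested.
- t_T and t_S are the shares of those episodes tested, and so excluded. The less-tested arm is set at 40%.
- d is the difference in testing between arms.

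**Formulas.** Untested episodes are counted, so the observed rates are p_T + c(1 − t_T) and p_S + c(1 − t_S). The risk difference shifts by c×d. Type I error is evaluated at the margin (0.50 versus 0.40 before miscounting) and power at 0.30 versus 0.40. Both use the formula above with the shifted rates and 120 per arm.

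Worked case, c = 5% and d = 20 points, arm T tested more: observed rates are 0.50 + 0.05×0.40 = 0.52 and 0.40 + 0.05×0.60 = 0.43, a difference of 0.09. SE = √((0.52×0.48 + 0.43×0.57)/120) = 0.0642. Type I error = Φ(0.01/0.0642 − 1.96) = 3.6%.

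| c | d (points) | Shift (points) | Type I error if T is tested more | Power if S is tested more |
|---|---|---|---|---|
| 2% | 0 | 0 | 2.5% | 90.0% |
| 2% | 10 | 0.2 | 2.7% | 89.4% |
| 2% | 20 | 0.4 | 2.9% | 88.9% |
| 5% | 0 | 0 | 2.5% | 89.4% |
| 5% | 10 | 0.5 | 3.0% | 87.9% |
| 5% | 20 | 1.0 | 3.6% | 86.3% |
| 10% | 50 | 5.0 | 11.8% | 66.7% |

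Rows with d = 0 show equal under-testing: type I error is unchanged and power falls slightly because non-target events are added to both arms. The last row is an extreme, shown only to mark the end of the scale.

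**The case against.** **The line has an ordinary reading.** It sits under component 1 and most naturally says that SARS-CoV-2 positivity, symptomatic or not, is not itself a qualifying event. A reader might infer that a bacterial or CMV infection in a positive patient is dropped, or that sites' testing choices decide in general whether infections count. The protocol does not say so: another infection meeting 1a-1c can be its own event, and two blinded specialists settle the diagnosis. What stands is that co-infection is not spelled out.

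**Much is already planned.** COVID-inclusive single components include infection, the only component that counting COVID-19 would change. The exclusion appears to leave deaths and graft losses from COVID-19 in the composite anyway. It would be wrong to conclude that the trial cannot examine robustness. Still, these endpoints are supportive only (10.3.5), and non-inferiority is decided on the composite. The SAP, which is not shown, may add the missing analysis; the endpoint wording, however, belongs to the protocol.

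**Nothing shows that testing differs by arm.** Randomisation is stratified by centre, so differences in local practice are balanced. Two-weekly calls, diaries, monitor screening and assessor queries improve ascertainment, and 6.17 names antigen tests and PCRs from respiratory material as of special interest. Unblinded investigators, with TTV results visible to them only in the active arm, make a difference possible; they are not evidence of one.

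**A COVID-inclusive composite is not free of testing effects.** A positive test can prompt antiviral treatment or reduced immunosuppression, and so create a 1b or 1c event. For the same reason an untested mild case may meet none of 1a-1c, which would make c small. Both points stand.

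**Conclusion.** The concern holds as a gap in a stated endpoint rule. Exclusion depends on a positive result from a test that is not required, the people choosing whether to test know the arm, co-infection is undefined, and the composite that decides non-inferiority has no listed COVID-inclusive counterpart.

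Its size cannot be derived from the protocol. With 2-5% of patients having a SARS-CoV-2 episode as their only event and a 10-20 point difference in testing, type I error at the margin is about 2.7-3.6%, or power falls to about 86-89% if the difference runs the other way. With equal testing, type I error stays at 2.5%. Larger distortions need inputs for which the documents give no support. The non-inferiority conclusion is not shown to be wrong; the point is worth correcting because the correction is cheap.

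**What to change.** 1. In 3.2 and the synopsis, define the exclusion by adjudicated cause. An episode is dropped only when the blinded assessors attribute it to SARS-CoV-2 alone. A separate infection meeting 1a-1c counts even if a SARS-CoV-2 test is positive. This settles co-infection; it does not recover tests that were not done.
2. In 3.3 and 10.3.3, name as a sensitivity analysis the primary composite with COVID-19 counted under 1a-1c, using the same difference, 95% confidence interval and 10-point margin. State that it removes the dependence on the exclusion but not every effect of testing, since a positive test can prompt treatment.
3. Optionally, record for each respiratory or febrile episode whether a SARS-CoV-2 test was done, and report testing by arm. This would show whether the condition for bias was present.

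Items 1 and 2 cost protocol wording and one extra analysis, using the existing assessors and data already collected. Item 3 costs one eCRF entry per episode. A mandatory additional test is not needed for this correction.

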## VISIT SCHEDULE

**Table 1 Trial-specific and routine procedures performed during the interventional trial.**

| Post-TX month                                     | 1          | 2  | 3  | 4 | 5 |    | 8  |    | 11 | 12 to 13 |
|---------------------------------------------------|------------|----|----|---|---|----|----|----|----|----------|
| Study week                                        | -12 to -11 | -8 | -4 | 0 | 6 | 12 | 18 | 24 | 30 | 36       |
| Study visit                                       | -3         | -2 | -1 | 1 | 2 | 3  | 4  | 5  | 6  | 7 (FUP)  |
| Informed consent                                  | X          |    |    |   |   |    |    |    |    |          |
| Inclusion/ exclusion criteria                     | X          |    |    | X |   |    |    |    |    |          |
| Intervention                                      |            |    |    | X | X | X  | X  | X  | X  |          |
| Medical History                                   | X          |    |    | X |   |    |    |    |    |          |
| Vital signs                                       |            |    |    | X | X | X  | X  | X  | X  | X        |
| Physical examination, body weight                 |            |    |    | X |   |    |    |    |    | X        |
| Pregnancy test                                    |            |    |    | X |   |    |    |    |    | X        |
| Medication                                        |            |    |    | X | X | X  | X  | X  | X  | X        |
| Adverse events a                       |            |    |    |   | X | X  | X  | X  | X  | X        |
| Primary end-point a                    |            |    |    |   | X | X  | X  | X  | X  | X        |
| Laboratory workup                                 |            |    |    |   |   |    |    |    |    |          |
| TTV R-GENE ®                           | X          | X  | X  | X | X | X  | X  | X  | X  | X        |
| TAC-trough level                                  |            | X  | X  | X | X | X  | X  | X  | X  | X        |
| Chemistry, CBC, vBGA, Urine analysis b |            | X  | X  | X | X | X  | X  | X  | X  | X        |
| BKV, CMV b                             |            |    |    | X | X | X  | X  | X  | X  | X        |
| DSA                                               |            |    |    | X |   |    |    |    |    | X        |
| Biobanking c                           |            |    |    |   |   |    |    |    |    |          |
| Whole blood, Serum, plasma, urine                 | X          | X  | X  | X | X | X  | X  | X  | X  | X        |
| Drug adherence d                       |            |    |    |   |   |    |    |    |    |          |
| MEMS ® BUTTON                          |            |    |    | X | X | X  | X  | X  | X  | X        |
| BAASIS                                            |            |    |    | X | X | X  | X  | X  | X  | X        |
| Patient diary                                     |            |    |    | X | X | X  | X  | X  | X  | X        |
| Claimed prescription check                        |            |    |    |   |   |    |    |    |    | X        |
| Psychological evaluation                          |            |    |    | X |   |    |    |    |    | X        |
| Quality of life                                   |            |    |    |   |   |    |    |    |    |          |
| SF-36, MTSOSD-59R                                 |            |    |    | X |   |    |    |    |    | X        |
| Protocol biopsy e                      |            |    |    | X |   |    |    |    |    | X        |

Note: BKV, BK virus; CBC, Complete blood count; CMV, Cytomegalovirus; DSA, Donor-specific antibodies; HLA, Human leucocyte antigen; FUP, follow-up; MTSOSD-59R, Modified Transplant Symptom Occurrence and Symptom Distress Scale 59R; rt-PCR, Real-time polymerase chain reaction; SF-36, Medical Outcomes Study Short Form 36; TAC, Tacrolimus; TTV, Torque Teno virus; TX Transplantation; vBGA, Venous blood gas analysis.

a Check-ups concerning infections and other adverse events will be performed additionally via telephone calls by study personnel every 2 weeks.

b Laboratory workup and virology screening will be performed not as part of the study protocol, but according to local centre standards. However, according to study protocol at least the leukocyte count, creatinine, and urinary protein- and albumin to creatinine ratio will have to be assessed. Other major laboratory parameters and findings concerning CMV and BKV screening including plasma CMV and BKV PCR performed routinely at the centres will be noted.

c Biological material will be stored for additional immunologic monitoring according to a sub-study.

d Adherence will be monitored during the trial by patient diary and evaluated at every visit; other assessment of adherence will be evaluated retrospectively.

e Protocol biopsies (including molecular microscope; MMDx) will not be performed as part of the study protocol, but according to local centre standards. However results on protocol biopsies obtained as part of the routine local centre standard will be noted. If part of the centre standard the month 3 protocol biopsy has to be performed before V1.

